### Sample size determination

The sample size was calculated according to the Simon’s minimax two-stage design, with PFS at 16 weeks as the primary endpoint. PFS is dichotomized according to whether PFS is ≤16 weeks (defined as disease control failure (DCF)) or > 16 weeks (defined as disease control success (DCS)). Therefore, treatment with mycophenolate mofetil will be considered successful if the 16-week radiological evaluation indicates stable disease, partial response, or complete response, as defined by the RECIST criteria version 1.1. Patients alive after 16 weeks without signs of progression will be regarded as DCS.

The sample size was calculated under a hypothesis of interest in which DCS at 16 weeks is ≥32% (*p*_1_ = 0.32, the minimal proportion of successes that makes the experimental treatment worth further studies) and a null hypothesis in which mycophenolate mofetil reaches a DCS at 16 weeks < 12% (*p*_0_ = 0.12, the proportion of successes that implies no clinically worthwhile activity of the experimental treatment). Setting *α* = 0.10 (where *α* represents the probability of failing to reject a treatment with response probability ≤*p*_0_) and *β* = 0.10 (where *β* represents the probability of rejecting a treatment with response rate ≥ *p*_1_), this condition requires 19 patients to be enrolled in Stage 1. Recruitment will continue to reach a total of 27 patients if the number of DCS among the first 19 patients is at least 3; otherwise, the trial will be stopped for inefficacy after analysis of 19 patients. As per the study protocol, mycophenolate mofetil will be deemed promising and worth further studies if at least 6 DCS is observed at the end of the study.

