SV = screening visit; C_x_w_y_ = cycle x week y; FV = final visit. ^(a)^ Lab tests include Na, K, Cl, HCO3, Ca, Mg, P, albumin, AST, ALT, ALP, total bilirubin, direct bilirubin, BUN, Cr, PT, PTT, INR, and LDH; ^(b)^ Blood obtained from the pharmacokinetic study will be used for measurement of circulating tumor cells on C_1_W_0_ and C_1_W_1_ so that no additional blood samples will be collected; ^(c)^ Urine analysis includes a urine pregnancy test for a female patient of childbearing age; ^(d)^ Blood samplings (at 0, 0.5, 1, 1.5, 2, 3, 4, 6, 8, 10, and 12 h); ^(e)^ Additional samplings for drug monitoring may be required when drug dosage is modified (after ≥7 days of drug administration with an adjusted dose level); ^(f)^ Tumor assessment by a computerized tomography (CT) scan (of the chest ± other organs, if required) or magnetic resonance imaging (MRI), done at baseline, 8 ± 1 weeks and 16 ± 1 weeks after initiation of study drug administration; in case of objective tumor response (complete response or partial response), confirmatory imaging studies will be performed at least 4 weeks after initial documentation of response

There are three drug regimens to be used for prophylaxis of possible infection during study participation: (1) ivermectin (12 mg/day) for 2 days before Cycle 1, Week 0 [28], (2) trimethoprim-sulfamethoxazole (160/800 mg/day) once daily from Cycle 1, Week 1, until discontinuation of mycophenolate mofetil [29], and (3) acyclovir (400 mg/day) twice daily from Cycle 1, Week 1, until discontinuation of mycophenolate mofetil [30]. No evidence of PK drug-drug interactions between any of these regimens and mycophenolate mofetil is reported [31].

Should mycophenolate mofetil prove beneficial to some patients (i.e., evidence of stable disease or partial response) at the end of the treatment period (on Week 16), the study treatment will be given to those patients in the extension period until one of the withdrawal criteria is met. Additional visits will be scheduled during the extension period (Table 4).

**Table 4 Tab4:** Additional visits and assessments in the extension period

Procedures	Study Visits								
	C_5_w_2_	C_5_w_4_	C_6_w_2_	C_6_w_4_	C_7_w_2_	C_7_w_4_	C_x_w_2_	C_x_w_4_	FV
Physical examination	×	×	×	×	×	×	×	×	×
Lab test for complete blood count	×	×	×	×	×	×	×	×	×
Other lab tests^(a)^		×		×		×		×	×
Circulating tumor cells	×		×		×		×		
Biobank collection		×		×		×		×	×
Urine analysis^(b)^		×		×		×		×	×
PK study^(c)^									

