### Statistical analysis plan

All patients who receive at least one dose of mycophenolate mofetil will be included in an intention-to-treat analysis. Patients’ baseline demographics will be summarized using descriptive statistics. Study drug administration will be described in terms of the total number of cycles (or days) administered, the median (range) of cycles (or days) administered, dose intensity, and reasons for deviations from planned therapy. Adverse events will be collected after the patient has taken the first dose of mycophenolate mofetil.

The PFS at 16 weeks or DCR (the primary endpoint) will be measured as a binary variable: DCS or DCF. The PFS and OS will be summarized using the Kaplan-Meier method and displayed graphically as appropriate. For patients lost to follow-up, they will be censored at the date of the last follow-up visit. Median PFS and OS (and their corresponding 95% confidence intervals) will also be provided.

All statistical analysis will be executed using IBM SPSS Statistics for Windows, version 22.0, with a *p* value of less than 0.05 considered to indicate statistical significance. It is possible that the decision rule of this single-arm, two-stage phase II clinical trial may need to be adapted from the original plan [33]. If the attained sample size at the end of this study is different from the one that is initially planned due to any reason, a statistical testing will be conducted by calculating the *p* value with the sample size at the stopping stage conditioned on the observed value [34, 35]. The Jennison-Turnbull confidence interval may be used by treating the observed sample size at the stopping stage like the planned sample size [36].

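### The primary endpoint has two success rules, a 16-week PFS cut-off and the 16-week scan result, that disagree when a scan in days 113–119 first shows progression; neither is given precedence

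*Protocol article*

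**What the plan says.** Three consecutive statements in the protocol article, Sample size determination, define success.

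- Date rule: "PFS is dichotomized according to whether PFS is ≤16 weeks (defined as disease control failure (DCF", against "> 16 weeks (defined as disease control success (DCS".
- Scan rule, introduced by *therefore*: treatment "will be considered successful if the 16-week radiological evaluation indicates stable disease, partial response, or complete response".
- Status rule: "Patients alive after 16 weeks without signs of progression will be regarded as DCS".

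The scan timing is in Study procedures, Table 3 footnote (f). Tumour assessments are at baseline and then at "8 ± 1 weeks and 16 ± 1 weeks after initiation of study drug administration".

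The Statistical analysis plan section adds only that "The PFS at 16 weeks or DCR (the primary endpoint) will be measured as a binary variable: DCS or DCF". Study endpoints and the Discussion use PFS at 16 weeks, disease control rate and disease stabilisation at 16 weeks as interchangeable terms. Both decisions use the resulting count: at least 3 DCS in the first 19 patients to continue, and at least 6 in 27 to call the drug promising.

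**The concern.** The word *therefore* treats the date rule and the scan rule as the same rule. They are the same only if every scan falls on day 112. With a window of days 105–119, a patient whose disease has grown can be a success or a failure depending on the appointment day and on which sentence the analyst follows.

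This is the primary endpoint, and the thresholds are small integers, so one or two reclassified patients can change the Stage 1 or the final decision. Only one assessment (week 8) is scheduled between baseline and week 16. Radiological progression arising between those two scans is therefore normally first seen on the scan whose date is in question. The trial is also open-label, so a choice between the rules made later could be made with the outcomes in view.

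**Working it through.** **1. The rules side by side.** Week 16 is 16 × 7 = day 112, and the window is 15 × 7 = day 105 to 17 × 7 = day 119. Progression is assumed to be dated at the scan that shows it. This is the usual convention, but the article does not state it.

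| Week-16 scan | Date rule | Scan rule |
|---|---|---|
| Progression, days 105–112 | DCF | DCF |
| Progression, days 113–119 | **DCS** | **DCF** |
| SD/PR/CR, days 113–119 | DCS | DCS |
| SD/PR/CR, days 105–112 | PFS > 16 weeks not yet shown | DCS |

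The status rule does not settle the second row. A patient scanned on day 115 passed day 112 with no documented progression, yet shows it at the evaluation.

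**2. The plan's own design.** Inputs from Sample size determination: p0 = 0.12, p1 = 0.32, α = β = 0.10; continue at ≥3/19, promising at ≥6/27. With X ~ Bin(19, p) and Y ~ Bin(8, p),

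P(promising) = Σ over x = 3…19 of P(X = x) · P(Y ≥ 6 − x).

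- p = 0.12: 0.0936 (type I error). Early stopping probability 0.597; expected sample size 19 + 8 × (1 − 0.597) = 22.2.
- p = 0.32: 0.9000 (power).
- An exhaustive search for the smallest total meeting both error limits returns the same design (stop at ≤2/19, reject the drug at ≤5/27).

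The stated design reproduces exactly.

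**3. Size if the date rule were applied.** Assume that 12% is the true rate under the scan rule and that PFS is exponential.

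- Progression-free at week 8: √0.12 = 0.346.
- Progressing between weeks 8 and 16: 0.346 − 0.120 = 0.226, or about 0.226 × 27 = 6.1 of 27 patients.
- If a share f of those patients' week-16 scans falls after day 112, the date-rule success rate is 0.12 + f × 0.226.

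| f (assumed) | Null success rate | P(promising) |
|---|---|---|
| 0 | 0.120 | 0.094 |
| 10% | 0.143 | 0.173 |
| 25% | 0.177 | 0.331 |
| 50% | 0.233 | 0.617 |

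**4. The same without a survival model.** Let g be the share of all patients whose progression is first seen on a scan after day 112. At a scan-rule rate of 12%, P(promising) is 0.163 for g = 2%, 0.298 for g = 5% and 0.554 for g = 10%. The values of g are also assumptions.

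**The case against.** **The text already points to one rule.** The scan rule is offered as the working consequence of the date rule. The next sentence asks for no signs of progression, the Discussion speaks of disease stabilisation at 16 weeks, and entry to the extension depends on stable disease or partial response at week 16. This stands as a reading of intent. It does not remove the conflict, because no sentence says that the scan result overrides the cut-off.

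**Event dating belongs in a fuller document.** This stands in part. Dating progression at nominal day 112 would make it PFS ≤16 weeks and remove the conflict over progressors. The missing dating convention is not the finding. The finding is that the article states two rules which differ under the usual convention.

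**The benchmark is itself a time-based rate.** The Discussion describes the analysis behind p0 as using PFS > 4 months. The documents therefore do not establish that 12% is a scan-rule rate, as step 3 assumes. This stands, and is one more reason to treat the figures as illustrative.

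**Stronger readings that a reader might infer, and that the documents do not support:**

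- *The sample size or type I error is wrong.* It is not; the design reproduces.
- *A larger effect.* Taking the 1.8-month median time to progression (Sample size justification) gives 49% progression-free at week 8. Setting 12% at week 16 then leaves 37% progressing between scans and P(promising) of 0.24, 0.52 or 0.87 for the same three shares. That joins two incompatible curves: an exponential with a 1.8-month median gives 24% at week 16, so about 25% progress between scans.
- *Investigators would book late scans to gain successes.* Nothing in the article suggests this.
- *Stable disease on days 105–111 is an equally serious gap.* Such patients continue in the extension, with visits in cycle 5 and further imaging at 12-week intervals, so later information is expected. The case is minor.

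**Conclusion.** The concern holds as a conflict between two stated rules for the primary endpoint, confined to progression first seen on an in-window scan on days 113–119 and dated at that scan. The scan rule is probably what was meant. If it governs, type I error stays at 0.094 and power at 0.900.

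If the date rule were used, even the mildest case shown (10% of affected scans late) would nearly double the false-positive probability, to 0.17, above the planned 0.10; 25% and 50% give 0.33 and 0.62. These figures rest on a single exponential, on assumed late-scan shares and on 12% being the scan-rule rate. They also treat all progression between the scans as first seen at week 16. Deaths and clinically detected progression before day 112 are failures under either rule and would lower the figures. The direction is firm; the size is not.

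**What to change.** State one governing rule for the binary endpoint in Sample size determination, and refer to it from Study endpoints and Statistical analysis plan:

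- DCS: stable disease, partial response or complete response on the week-16 scan done within its window, with no earlier progression or death.
- Progression on that scan: DCF, whatever its calendar day.
- Dated PFS: kept for the Kaplan-Meier analysis.

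Keep a note that the benchmark behind p0 is defined as PFS > 4 months, so that readers can see how the endpoint relates to the historical rate.

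The cost is wording only. Sample size, thresholds, visits and scan window are unchanged. The rule should be fixed before the Stage 1 successes are counted.

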## Background

Osteosarcoma is one of the most common primary malignant tumors of the bone in adolescents and young adults, with the incidence of approximately 2–4 per million worldwide [1–4]. The substantial advance in the treatment of osteosarcoma occurs in the 1970s and 1980s, when chemotherapy was shown to significantly improve the survival outcome of the patients with localized disease undergoing surgical resection [5, 6]. However, little further progress has been observed since then, with a 5-year overall survival remaining at approximately 70 and 30% in patients with localized and metastatic disease at diagnosis, respectively [7, 8]. At present, the combination of surgical resection and systemic chemotherapy with, at least, three active drugs (i.e., doxorubicin, cisplatin, and high-dose methotrexate) remains the standard treatment for patients with osteosarcoma [9–11].

Mycophenolate mofetil is an immunosuppressive agent currently being used for the prophylaxis of organ rejection following transplantation [12, 13]. It is a prodrug of mycophenolic acid (MPA), a potent inhibitor of inosine monophosphate dehydrogenase (IMPDH) [14, 15]. In some cancer in which IMPDH is upregulated, MPA may possess anti-cancer activity [16]. In 2010, Fellenberg et al. reported the observed overexpression of IMPDH in metastatic and chemo-resistant osteosarcoma cell lines, and pharmacological inhibition of IMPDH could result in a reduction of cell viability and cell proliferation [17]. A recent in vitro study has revealed the anticancer activity of MPA against osteosarcoma cell lines, with the half maximal inhibitory concentration (IC_50_) of 0.46–7.30 μM across all tested cell lines [18]. The in vivo experiment has shown the inhibition of tumor growth and lung metastasis of osteosarcoma in mice treated with mycophenolate mofetil [18]. As a result, mycophenolate mofetil has been recently proposed to be a promising new drug candidate for the treatment of osteosarcoma [19].

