## Methods/design

### Study objectives

The primary objective of this study is to assess the anticancer activity of mycophenolate mofetil in patients with high-grade locally advanced or metastatic osteosarcoma, and the secondary objective is to assess the safety and tolerability of the drug. The present study also aims to explore the pharmacokinetics of mycophenolate mofetil, biomarkers, and the quality of life in patients with high-grade locally advanced or metastatic osteosarcoma.

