### Interventions

Mycophenolate mofetil (CellCept®, Roche Laboratories Inc., Nutley, New Jersey) in 500 mg/tablet will be used in this trial. All adult patients (aged ≥18 years) will be treated with mycophenolate mofetil at the initial dose of 5 g/day, twice daily, while adolescent patients (aged 13–17 years) will be treated with mycophenolate mofetil at the initial dose of 3–5 g/day based on the patient’s body surface area (BSA) at enrollment (i.e., 5 g/day for those with a BSA of > 1.5 m^2^, 4 g/day for those with a BSA of 1.26 to 1.5 m^2^, and 3 g/day for those with a BSA of 1.0–1.25 m^2^). Self-administration of the study drug will take place on an outpatient basis (under parents’ supervision in some cases, as appropriate). Patients will return unused tablets at each follow-up visit; the unused tablets will be counted and recorded to determine compliance. One cycle is considered to be 4 weeks, and the next cycle of the treatment with mycophenolate mofetil will start only after safety assessments are done.

Allopurinol at the dose of 300–600 mg/day will be coadministered orally, twice daily, for blockage of the guanine salvage pathway [23]. All adult patients (aged ≥18 years) will be treated with allopurinol at the dose of 600 mg/day twice daily, while adolescent patients (aged 13–17 years) will be treated with allopurinol at the dose of 300 or 600 mg/day twice daily based on the patient’s body weight at enrollment (i.e., 600 mg/day for those with a body weight of ≥40 kg, and 300 mg/day for those with a body weight of < 40 kg). Evidence in kidney transplant recipients suggests that concurrent administration of mycophenolate mofetil with allopurinol is innocuous [24, 25].

Available palliative and supportive care for disease-related symptoms should be offered to all patients. Palliative radiotherapy is allowed for local pain control, provided that (1) the patient does not have progressive disease, (2) no more than 10% of the patient’s bone marrow is irradiated, and (3) the radiation field does not encompass a target lesion. Surgical resection of the disease is permitted after documentation of response. All the patients will be instructed not to take any other medications (including over-the-counter products) during study participation without prior consultation with the investigators.

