### Justification for the study design and study endpoints

In phase II osteosarcoma trials, a single-arm design may be preferred to a randomized-controlled design owing to the fact that osteosarcoma is a rare disease, with a limited number of patients available to be enrolled in early-phase clinical trials with a specific and strict set of eligibility criteria [38]. Based on a systematic review of past experience, most phase II osteosarcoma trials are conducted using a single-arm, two-stage design [39]. A single-arm design is considered appropriate for the evaluation of monotherapy when a well-defined historical control database is available, while a key limitation of this approach is that any changes in patient management over time may shift the expected outcome (e.g., PFS) above the historical benchmark [40]. In the case of osteosarcoma, the standard treatment for newly diagnosed and recurrent disease has not substantially been changed over the past three decades, so that the historical benchmark for the outcome of patients could be reliably used [41].

One of the major characteristics of osteosarcoma is that tumor volume shrinkage, determined by radiographic imaging, may not reflect the efficacy of an anticancer agent at the cellular level since tumor tissue is customarily substituted by the calcified matrix [42]. Even if the treatment is effective, the calcified matrix may still prevent volume reduction of the tumor [43]. Hence, objective radiographic responses in osteosarcoma are rarely observed, even with proven complete necrosis in the tumor after neoadjuvant chemotherapy [44]. In addition, the chance of spontaneous stability in advanced osteosarcoma is estimated to be extremely low [45]. Therefore, it may be reasonable to regard ‘stable disease’, rather than only ‘complete response’ and ‘partial response’, at a pre-specified, justified period as an appropriate surrogate endpoint in this specific group of population [39]. This is in agreement with the recent analysis of seven phase II osteosarcoma trials, where PFS > 4 months (defined as DCS) is used as a primary endpoint [44]. It is, thus, reasonable to consider PFS at 16 weeks (or disease stabilization at 16 weeks) as a success in this ESMMO trial setting where a decrease of tumor volume is not expected.

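### Every patient takes allopurinol with mycophenolate mofetil, but the objectives, hypotheses and decision rules name mycophenolate alone; a positive result supports only the pair

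*Protocol article*

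**What the plan says.** **The treatment.** The Interventions section of the Protocol article describes two drugs. Allopurinol "will be coadministered orally, twice daily, for blockage of the guanine salvage pathway". Its coverage is complete: "All adult patients (aged ≥18 years) will be treated with allopurinol at the dose of 600 mg/day twice daily", and adolescents "will be treated with allopurinol at the dose of 300 or 600 mg/day twice daily based on the patient’s body weight at enrollment". It is not among the three prophylactic regimens listed under Study procedures, nor in the supportive-care paragraph of Interventions. Exclusion criteria bar patients who are allergic to allopurinol or cannot take it. The Background names IMPDH inhibition as the action of mycophenolic acid.

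**The claim.** The primary objective is "to assess the anticancer activity of mycophenolate mofetil in patients with high-grade locally advanced or metastatic osteosarcoma"; the secondary objective is the safety and tolerability of that one drug. In Sample size determination the null hypothesis is stated for mycophenolate, and the final rule reads "mycophenolate mofetil will be deemed promising and worth further studies if at least 6 DCS is observed". Stopping rules frames the stage 1 look (at least 3 successes in 19) in the same way. Sample size justification defines p0 = 0.12 as the rate to be expected here if mycophenolate does nothing. The methods part of the Abstract does not mention allopurinol.

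**The design argument.** Justification for the study design and study endpoints says "A single-arm design is considered appropriate for the evaluation of monotherapy", on condition that a good historical database exists.

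**The concern.** The treatment described in Interventions is not the treatment that the objectives and decision rules judge. Allopurinol is given to act on the same nucleotide supply that mycophenolate is meant to cut, so it could contribute to disease control at 16 weeks. If it does, a positive result belongs to the pair, while the protocol would report it as a property of mycophenolate.

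This matters because the Background names a randomized phase III trial as the next step, and the Abstract says that the results will show whether mycophenolate merits further development. Someone who took the stated conclusion at its word could carry forward a regimen that this trial never gave. The safety objective has the same mismatch: tolerability observed here is that of the pair.

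**Working it through.** **Inputs** (Sample size determination): p0 = 0.12, p1 = 0.32, α = 0.10, β = 0.10; stage 1 n = 19, continue with at least 3 successes; total 27, positive with at least 6.

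**Step 1. Reproduce the design.** With b(x; n, p) the binomial probability,

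Pr(go | p) = Σ over x = 3 to 19 of b(x; 19, p) × Pr[Bin(8, p) ≥ max(0, 6 − x)].

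- At p = 0.12: 0.0936 (limit 0.10).
- At p = 0.32: 0.9000 (required 0.90).
- Probability of stopping after stage 1 at p = 0.12: 0.597.
- Expected sample size at p = 0.12: 19 + 8 × (1 − 0.597) = 22.2.

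A search over totals from 20 to 35 found 27 to be the smallest that meets both limits. The sample size and cut-offs are right as stated.

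**Step 2. Ask whose rate p is.** Let θ(M+A) be the success rate with mycophenolate plus allopurinol, and θ(M) the rate with mycophenolate alone. All 27 patients take both drugs, so 27 − 27 = 0 inform θ(M). The formula above contains only θ(M+A). The same holds for p0: the rate in this trial if mycophenolate did nothing would be the rate on allopurinol alone, and that equals the historical 12% only if allopurinol adds nothing. The article does not state or discuss that assumption.

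**Step 3. Show what the rule responds to.**

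| Assumed θ(M+A) | Pr(mycophenolate declared promising) |
|---|---|
| 12% | 0.094 |
| 15% | 0.204 |
| 19% | 0.400 |
| 25% | 0.691 |
| 32% | 0.900 |

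These probabilities hold whatever θ(M) is. The documents give no rate for mycophenolate alone and no size for any contribution from allopurinol, so any pairing of the two rates is an assumption. Suppose θ(M) is 12%. If the pair reaches 15% to 19%, mycophenolate is declared promising with probability 0.20 to 0.40; if it reaches 32%, with probability 0.90. The 10% error limit protects a statement about the pair, not one about mycophenolate alone.

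**Step 4. Look at the two directions separately.** Assume that allopurinol does not weaken mycophenolate, so that θ(M) ≤ θ(M+A). A low θ(M+A) then also implies a low θ(M), and a negative result counts against mycophenolate. A high θ(M+A) leaves θ(M) free to lie anywhere below it. The attribution problem therefore sits in the positive direction.

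**Step 5. Look for text that closes the gap.** The activity evidence described in the Background, and the dose rationale in the Discussion, concern mycophenolic acid or mycophenolate and do not mention allopurinol. The only remark on the pair is about safety in kidney transplant recipients. No section limits the conclusion to the combination or says that allopurinol cannot affect the endpoint.

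**The case against.** The best defence is that mycophenolate is shorthand for the regimen. Interventions sets out openly what every patient takes, Sample size determination also describes p0 and p1 as rates for the experimental treatment, and a phase II screening decision does not assert that the drug works unaided. Nor does any section attribute antitumour activity to allopurinol; that it supports the effect is inferred from its stated purpose together with the IMPDH mechanism. This stands in part: the comparison with 12% is sound for the regimen and nothing needs redesign. It does not remove the point, because the objectives, hypotheses and rules are printed in full and none of them mentions the second drug.

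Some stronger readings are tempting but unsupported:

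- **That the single-arm design rests on this being a monotherapy trial.** The sentence is a general one with a citation, tied to the availability of historical data. The section also argues from the rarity of the disease, from common practice and from stable benchmarks. It sits badly with a two-drug regimen, but it does not call this trial a monotherapy trial.
- **That a negative result says nothing about mycophenolate.** If allopurinol was added to help, failure of the pair is also evidence against mycophenolate.
- **That adverse events will be blamed on mycophenolate.** The dose tables adjust only mycophenolate, but no section says how causality is assigned.
- **That allopurinol exposure will go unrecorded.** Tablet counts, dose intensity and attribution for each drug are details that an article may leave to the full protocol, and concomitant medication is reviewed at every visit.

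**Conclusion.** The point holds as a fault of attribution in the stated objectives, hypotheses and decision rules. It affects all 27 patients: none supplies information on mycophenolate without allopurinol, so a positive result supports mycophenolate given with allopurinol and nothing narrower. A reader might infer that the trial can draw no valid conclusion. That goes too far: the test of the regimen against 12% keeps its exact type I error of 0.0936 and power of 0.9000.

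The conclusion rests on the purpose given for allopurinol and on the absence of any statement that it cannot affect the endpoint. The size of any contribution is unknown, and the probabilities quoted for particular pairings of rates are illustrations. That a negative result still counts against mycophenolate assumes that allopurinol does not reduce its effect. The correction is worth making because it changes what the trial may claim.

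**What to change.** - State the primary and secondary objectives, the null and alternative hypotheses, the rules of at least 3 in 19 and at least 6 in 27, and the planned conclusion for mycophenolate mofetil given with allopurinol. Word the meaning of p0 to match.
- Add a sentence that the separate contributions of the two drugs to efficacy and to toxicity cannot be estimated from this design.
- Reconcile the general monotherapy argument in Justification for the study design and study endpoints with the two-drug regimen in Interventions, for example by resting the single-arm choice on the other grounds already given there.

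This needs no extra patients, visits or analyses, and 19/27 with cut-offs 3 and 6 stay as they are. The cost is a narrower claim. No view is taken here on whether allopurinol should be given or at what dose.
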